**Figure 2 F2:**
[figure not shown]
Participants’ flow through the study.

The design of this study is according to the guidelines specified by the Task force on promotion and dissemination (1995) and approved by the independent Medical Ethics Committee (METC) of the Utrecht Medical Centre at Utrecht University.

#### Sample size

Based on previous research [16] an effect size (Cohen’s d) of 0.53 is expected. Power calculations indicated that 70 adolescents per condition (assuming an alpha of 0.05, a statistical power, 1-beta, of 0.80 and a drop-out of 20%; power calculations in STATA) are required to detect a difference in depression diagnosis. In total 140 adolescents will be included.

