## Background

Depressive disorders in adolescents are among the most prevalent disorders with a high burden of disease [1] and high risk of recurrence [2,3]. Before entering adulthood, 14 to 25% of the adolescents have experienced at least one episode of a depressive disorder [2]. Besides the high prevalence [4-7], comorbid psychiatric diagnoses are often present [8-10]. In addition, a heightened risk exists for development of social problems, juridical problems, learning problems, substance abuse, negative life events, physical problems, teen pregnancies and suicide [2,9,11]. Therefore, it is important that depression is treated in an early stage with an effective treatment [2,12].

In the international literature, there is no consensus on the degree of effectiveness of psychotherapeutic interventions in depressed adolescents. In a meta-analysis, which included studies with a large diversity of investigated interventions, only a modest effect size of 0.34 was found [13]. Other meta-analyses calculated medium (0.72) [14] to large (1.27) effect sizes [15]. In a meta-analysis solely directed at Cognitive Behavioral Therapy (CBT) a medium effect size of 0.53 was found [16]. Although the effect size for CBT is promising, it also reflects the need for improved treatment of depression, as a large group of depressed adolescents will not recover after CBT treatment.

In addition, it is often discussed that effectiveness studies in depressed adolescents lack generalizability for clinical practice, because the study samples do not match the complex and severe cases in routine mental health care [13]. In this study, this issue is addressed by comparing CBT to treatment as usual within a referred clinically depressed group of adolescents.

Within this study an individual revision of the group CBT program “Coping with Depression course for Adolescents” (CWD-A) [17] will be investigated. Group CBT was adapted into an individual CBT format because it is much better applicable within mental health care than group CBT, for instance children can start treatment immediately. Several RCT’s were conducted with an American population, but not with clinically referred adolescents. Results repeatedly have shown that the CWD-A was more effective than control conditions [18,19] and treatment as usual [20,21]. As only one research group investigated the CWD-A, it is regarded as probably efficacious [22].

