### Statistical analyses

Missing values will be imputed. Intent-to-treat as well as completer analyses will be conducted. The effect of the intervention is analyzed with a chi-square test on the dichotomous primary outcome measure, presence of the depression diagnosis (K-SADS-PL). The cost-effectiveness analyses will be based on the comparison of costs and effects in both conditions and will be done according the international guidelines [70]. The cost- effectiveness analyses will be done separately from the perspective of mental health and society over a period of 6 months and 1 year. The effects of societal costs will be expressed in years to live, corrected for quality of life (QALYs). The costs of CBT versus CAU will be expressed in 1) incremental costs per QALY and 2) incremental costs per adolescent with a depression in full remission.

The secondary continuous outcome measures will be analyzed with repeated measures MANCOVA using the pre-test as a covariate as is recommended for RCT’s with pre-, post- and follow-up measurements [71]. For each questionnaire, the effect size (Cohen’s d) from pre- to post-treatment is defined as (M_pre_-M_post_)/SD_pooled_, where SD_pooled_ = [(SD_pre_^2^ + SD_post_^2^)/2]. CBT versus TAU pre-post effect sizes are calculated as follows [(M_CBT post_-M_TAU post_)/SD_pooled post_] – [ (M_CBT pre_-M_TAU pre_)/SD_pooled pre_]. Furthermore, analyzes will be conducted to establish clinical significance and the reliable change index [72].

Moderators will be analysed by multi-group analyses for dichotomous variables. The continuous variables will be analysed using hierarchic regression analyses. Mediator effects will be analysed using hierarchical regression analyses and structural equation modelling.

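### The 70 per arm follows from a comparison of two means with Cohen's d = 0.53, so the stated 80% power is not supported for the primary chi-square test on diagnosis

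*Protocol article*

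**What the plan says.** All the inputs are in the Sample size section of the protocol article. The effect is given as "an effect size (Cohen’s d) of 0.53 is expected". The other inputs are "assuming an alpha of 0.05", "a statistical power, 1-beta, of 0.80" and 20% drop-out. The result is "Power calculations indicated that 70 adolescents per condition", and the endpoint it serves is named in the same sentence: "a drop-out of 20%; power calculations in STATA) are required to detect a difference in depression diagnosis".

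The Background describes the source of the effect size as a meta-analysis "solely directed at Cognitive Behavioral Therapy (CBT) a medium effect size of 0.53 was found".

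The Statistical analyses section plans "a chi-square test on the dichotomous primary outcome measure, presence of the depression diagnosis (K-SADS-PL". It also defines Cohen's d for this trial, as a difference of means divided by a pooled standard deviation.

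The article states no expected diagnosis rate in either arm, no risk difference or odds ratio, and no conversion from d to proportions.

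**The concern.** Cohen's d is a standardised difference of means. It sizes a comparison of means and does not by itself determine the power of a comparison of two proportions. That power also depends on the diagnosis rate in the TAU arm and on how a shift on a symptom scale translates into fewer diagnoses. If diagnosis behaves like a cut on an underlying severity scale, the yes/no version carries less information than the scale, and the same number of patients gives less power.

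This is the article's only power statement for its primary endpoint. If the power for diagnosis is lower than stated, the chance of missing an effect of the assumed size exceeds 20%. A reader who takes the 80% at face value would then give a non-significant primary result too much weight.

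**Working it through.** **Step 1. Reproduce the plan's figure.** Inputs from the Sample size section: d = 0.53, alpha 0.05, power 0.80, drop-out 20%. Sidedness is not stated; two-sided is assumed.

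n per arm = 2 × (1.960 + 0.842)² / 0.53² = 55.9, rounded up to 56. Allowing for drop-out: 56 / 0.80 = 70. This is the stated figure exactly. Variants do not match: a one-sided test gives 45, then 57; a t-based calculation gives 57, then 72.

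**Step 2. Translate d = 0.53 into diagnosis-free proportions.** The article gives no rates, so the TAU diagnosis-free rate p is an assumption and is varied. Two usual conversions are used:

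- Logistic: OR = exp(0.53 × π/√3) ≈ 2.6, applied to the odds p/(1 − p).
- Latent normal: CBT rate = Φ(Φ⁻¹(p) + 0.53).

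**Step 3. Power of the planned test.** Uncorrected Pearson chi-square at 5%, by full enumeration of the two binomial distributions. The plan's own evaluable number is 56 per arm.

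| Assumed TAU diagnosis-free rate | Logistic: CBT rate | Logistic: power | Latent normal: CBT rate | Latent normal: power |
|---|---|---|---|---|
| 10% | 22% | 44% | 23% | 45% |
| 20% | 39% | 63% | 38% | 55% |
| 30% | 53% | 69% | 50% | 59% |
| 40% | 63% | 70% | 61% | 60% |
| 50% | 72% | 68% | 70% | 58% |
| 60% | 80% | 63% | 78% | 57% |
| 70% | 86% | 54% | 85% | 51% |
| 80% | 91% | 40% | 91% | 42% |

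For rates of 20-70%, power is 54-70% (logistic) and 51-60% (latent normal). No rate tried reaches 80%.

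**Step 4. Sensitivity to the evaluable number.** With all 70 per arm contributing full information and rates of 20-70%, power is 64-81% (logistic) and 60-71% (latent normal). It reaches 80% only near a 40% rate under the logistic conversion.

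**Step 5. Sensitivity to the meaning of 0.53.** If 0.53 were Cohen's h (the arcsine difference between two proportions), the formula would also give 2 × (1.960 + 0.842)² / 0.53² = 55.9, then 56, then 70. Chi-square power at 56 per arm would be about 79-80% for TAU rates of 10-80%.

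**Step 6. Difference detectable with 80% power at 56 per arm**, by the same enumeration: 30% vs about 56.2%, 40% vs 66.4%, 50% vs 75.4%, 60% vs 83.4%. That is about 23-26 percentage points. Rounded down to 50% vs 75%, power is 79%, just short of the target.

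**The case against.** **The exact match to 70 does not prove the route.** Cohen's h = 0.53 leads to the same 56 and 70, and would make the 80% right for the chi-square. This stands as a possibility but not as the natural reading. The text says Cohen's d, takes it from a meta-analysis, and elsewhere defines d through means and standard deviations. If h was used, the Sample size section mislabels its input and still needs correcting.

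**The power is not known to be 51-70%.** A reader might infer from the table that the trial really has 51-70% power and a 30-49% risk of missing the effect. The documents do not support that. They give no diagnosis rates and no conversion from d. The K-SADS-PL diagnosis combines adolescent, parent and clinician views, and nothing shows it to be a cut of the scale on which 0.53 was measured. The lower end also depends on where the grid of rates stops, since power falls to about 40-45% at 10% or 80% diagnosis-free. This objection stands, and the figures are an illustration only.

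**Imputation keeps all 70 in the analysis.** The Statistical analyses section does plan imputation and intention-to-treat. Imputing does not restore the lost information, and the plan itself inflates for 20% loss. Even with 70 fully informative patients per arm, power mostly stays below 80%.

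**A condensed article may leave the rates to a fuller document.** That is fair as to their absence, which is not itself the finding. The finding is that the input, the number and the endpoint stated together do not fit.

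**The Discussion says power was raised to allow for a smaller effect against active TAU.** The reproduced figure shows no such margin: 70 is the unreduced d = 0.53 at exactly 80%.

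**Conclusion.** The point holds as a mismatch between the calculation and the primary test. The arithmetic is correct for comparing two means with d = 0.53, but the result is presented as sufficient for a difference in diagnosis, and the stated 80% is not supported for the chi-square.

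The size of the shortfall is conditional. It rests on a two-sided 5% test, 56 evaluable per arm, an effect on diagnosis equivalent to d = 0.53, and an assumed TAU diagnosis-free rate. On those assumptions power is about 51-70% for rates of 20-70%, lower outside that range, and 60-81% for rates of 20-70% if nobody is lost. Power is probably below 80%; by how much cannot be settled from the documents.

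**What to change.** Keep N = 140 and rewrite the Sample size section in two parts.

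- Tie the 80% power at d = 0.53 to a continuous measure such as the CDI-2, for which the calculation is valid.
- For the primary K-SADS-PL diagnosis, have the authors state the CBT and TAU diagnosis rates they assume. They should then give the chi-square power with 56 evaluable per arm and the difference detectable with 80% power: roughly 25 percentage points, for example slightly more than 50% vs 75%. Any range should be presented as conditional on the assumed rates and on the conversion from d.

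If 0.53 was in fact entered as Cohen's h, the section should say so and give the proportions behind it.

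The change is to wording only, with no extra patients and no change to the analysis. The cost is that the stated power for the primary endpoint becomes less favourable.

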#### Study sample

In total 140 referred clinically depressed adolescents aged 12 to 21 (*n* = 140) and their parents will be included in this study. If the adolescent is 18 years or older, parents will only be approached after the adolescent’s permission. The inclusion criteria for the depressive adolescents are: (1) a primary diagnoses of Depressive Disorder (regardless the severity: mild, moderate or severe) or Dysthymic disorder, (2) age 12 to 21 years, and (3) referred to one of the participating mental health institutions. The exclusion criteria are: (1) acute suicide risk, (2) drug abuse (as primary diagnosis), (3) pervasive developmental disorder (as primary diagnosis), (4) bipolar disorder (as primary diagnosis), (5) day care or admission to the clinical setting and (6) not fluent in Dutch, Turkish, Arabic or Berber language. If medication is used (for the depression or another disorder), the dosage should be kept constant during the intervention, unless medication is the control treatment.

Participants in both groups will be compared afterwards for their match on the following characteristics: age, ethnicity, gender, educational level parents and severity of the depression. If significant differences between two groups appear, these variables will be controlled for in analyses.

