#### Design

This study is designed as a multi-site, randomized controlled clinical trial in which individual CBT will be compared to TAU. Four multiple informant (adolescent, parent, therapist) assessments are done: prior to treatment (pre-test assessment), immediately after treatment (post-test assessment or after 15 sessions), 6 months after treatment (6 month follow-up) and 1 year after treatment (1 year follow-up). To investigate potential mediators two temporary assessments are conducted, each after 5 therapy sessions.

All sessions will take place within routine outpatient care within second order public mental health clinics to enhance external validity. All treatments in both conditions are delivered by psychologists with at least a master's degree-level and two years of experience within professional mental health care. These professionals are trained before delivering the treatments to enhance treatment integrity.

Adolescents who are diagnosed with a depression according to the K-SADS-PL [26,27], who meet inclusion criteria and do not meet the exclusion criteria are randomly assigned to either individual CBT or TAU. Random assignment per adolescent is executed using computer generated block randomisation and stratified per mental health centre. See Figure 2 for patient’s flow chart.

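### The primary chi-square test cannot follow the plan's rule to adjust for baseline variables that differ significantly, so the primary analysis is not fixed and the power from adjusting for severity is given up

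*Protocol article*

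**What the plan says.** All places are in the protocol article.

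- **Study sample.** The arms are to be "compared afterwards for their match on the following characteristics: age, ethnicity, gender, educational level parents and severity of the depression". The consequence follows directly: "If significant differences between two groups appear, these variables will be controlled for in analyses". No significance level is given, and nothing limits the rule to particular outcomes.
- **Statistical analyses, primary outcome.** "The effect of the intervention is analyzed with a chi-square test on the dichotomous primary outcome measure, presence of the depression diagnosis (K-SADS-PL"). No stratified or model-based version is named.
- **Statistical analyses, secondary outcomes.** "The secondary continuous outcome measures will be analyzed with repeated measures MANCOVA using the pre-test as a covariate". Here the pre-test enters whatever the observed balance.
- **Design.** "Random assignment per adolescent is executed using computer generated block randomisation and stratified per mental health centre". Centre is the stratification factor and is not among the five listed characteristics.
- **Table 1.** K-SADS depression severity is collected at pre-test.

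**The concern.** There are two faults, and they compound each other.

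First, the rule picks covariates by the wrong criterion. Under computer-generated allocation a significant baseline difference is a chance event. Its p-value says nothing about whether the variable predicts later diagnosis. A strongly prognostic imbalance just short of significance goes unadjusted, while a significant but irrelevant one is adjusted for.

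Second, the rule and the primary test do not fit together. A chi-square on a two-by-two table cannot control for age or severity. If the rule triggers, someone must choose another primary model, its form and its effect measure with the data in hand. Which analysis is primary then depends on the observed sample.

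At stake are the pre-specification of the main result and the precision that baseline severity could supply. Severity is plausibly the most prognostic of the five, yet it would enter the primary analysis only by accident.

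**Working it through.** **1. The plan's own figure.** From the Sample size section, "an effect size (Cohen’s d) of 0.53 is expected", "assuming an alpha of 0.05, a statistical power, 1-beta, of 0.80 and a drop-out of 20%; power calculations in STATA". Taking alpha as two-sided (the article does not say):

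n = 2(1.960 + 0.842)² / 0.53² = 55.9, so 56 per arm; 56 / 0.80 = 70 per arm.

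The stated 70 is reproduced and is not in dispute here. It gives 2 × 56 = 112 adolescents expected to have outcome data.

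**2. How often the rule would trigger by chance.** There are five characteristics. The level is assumed to be 0.05 and the tests independent:

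1 − 0.95⁵ = 0.226, about 23%.

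At an assumed level of 0.10 it is 1 − 0.90⁵ = 0.410. Correlation among the five lowers both figures.

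**3. What the rule does to power and error rate.** Simulation inputs:

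- From the article: 14 centres, and 112 analysed (8 per centre).
- Derived: d = 0.53 converted to a log odds ratio, 0.53 × π/√3 = 0.96 (odds ratio 2.6).
- Assumed: severity as a continuous covariate with log odds ratio 0.6 or 1.0 per SD, and some variation between centres.

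| Primary analysis | Power, severity 0.6 per SD | Power, severity 1.0 per SD |
|---|---|---|
| Chi-square, never adjusted | 60% | 49% |
| Adjust for severity only if its baseline test has p < 0.05 | 60% | 49% |
| Logistic regression, severity always included | 66% | 57% |

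Type I error was about 3 to 5% for all three. A repeat run (6,000 trials per setting, intercept 0.3 on the log-odds scale, centre SD 0.5 and 0.8) gave 59% and 47% for the first row, 59% and 47% for the second, and 63% and 54% for the third. The gain from fixed adjustment is therefore roughly 4 to 8 percentage points. The triggered rule gains almost nothing because a given covariate triggers it in only about 5% of trials.

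A second setting (56 per arm, log odds treatment effect −1.0, no centre effect, severity 0.5, 1.0 and 1.5 per SD) shows the same pattern. Power is 67%, 54% and 43% unadjusted; 67%, 55% and 44% triggered; 70%, 63% and 57% with fixed adjustment. Type I error under the trigger was 4.0%, 4.3% and 3.7%.

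Only the differences between rows bear on this point. That all rows lie below 80% is not caused by the adjustment rule.

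**4. How centre may enter.** Adding 14 centre indicators as fixed effects to the severity model, with about 8 analysed per centre, raised type I error to about 7 to 8%. The repeat run gave 6.8% and 7.1%. The severity-only model stayed at about 4%.

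**The case against.** **The rule is workable for most outcomes.** A reader might infer that covariates enter every analysis only through the trigger, or that the rule cannot be carried out anywhere. The article does not support this. The secondary MANCOVA always includes the pre-test and can take any flagged variable. The conflict is confined to the primary binary outcome.

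**A chi-square can be stratified.** A Cochran-Mantel-Haenszel test could handle categorical characteristics such as gender. That is true, but the article does not name it, and continuous age would first need cut-points.

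**The trigger protects against the worst imbalances.** This has some force. In the second setting with no treatment effect, among the roughly 5% of trials with a significant severity imbalance, the chi-square rejected in 9%, 15% and 18%. Adjustment is useful in those trials, but adjusting in every trial covers them too and needs no choice after the data are seen.

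**Nothing is invalid.** A reader might infer that a data-driven rule inflates type I error. Overall it does not, as the simulations show.

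**Imbalance could bias the effect size.** With 70 per arm, a severity difference of up to 0.33 SD passes as non-significant, and a reader might carry this through as a shift in the d of 0.53. That does not hold here. It is a worst case on a continuous scale with assumed correlations, the primary outcome is binary, and the continuous outcomes already carry their own pre-test.

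**This is an article, not an analysis plan.** The detail of an adjusted model is commonly left to the analysis plan, and its absence is not the point. The point is a rule that the article does state, and that does not fit the primary test it also states.

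**Conclusion.** The point holds for the primary outcome only. The article applies a significance-triggered adjustment rule to its analyses without restriction, and names a primary test that cannot obey it. The rule would be triggered by chance in about 23% of trials, assuming five independent tests at 0.05.

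The cost is an unfixed primary analysis and a moderate loss of power: about 60% and 49% under either the chi-square or the triggered rule, against about 66% and 57% with severity always included. These powers rest on an assumed severity effect of 0.6 to 1.0 per SD, the conversion of d to a log odds ratio, and a continuous severity score. A weaker severity effect, or severity graded only as mild, moderate or severe, would give a smaller gain. The contradiction between the two statements depends on none of these assumptions. It should be corrected, but it does not make the trial's main test invalid.

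**What to change.** - Delete the rule that significant baseline differences determine adjustment, and present baseline characteristics descriptively.
- Pre-specify the primary analysis as a logistic regression of K-SADS-PL depression diagnosis on arm and baseline depression severity, used whatever the observed balance. Report the standardised risk difference with its 95% confidence interval.
- Keep the chi-square test as an unadjusted sensitivity analysis.
- If centre is included because allocation was stratified by it, use a random intercept, conditional logistic regression or a stratified test. Do not enter 14 fixed centre effects.
- If any of the other four characteristics is wanted in the model, name it now.

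The cost is a change of wording. Severity is already collected at pre-test, so no new data, visits or participants are needed.

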#### Recruitment

The participants are recruited from fourteen different specialized mental health care institutions spread all over the Netherlands. An experienced psychologist within the mental health centre informs the adolescents and their parents about the study. After written informed consent by the adolescent and his/her parents, a trained independent researcher carries out an interview to check for the inclusion and exclusion criteria.

